## Randomization

Based on the sample size calculation, a total number of 88 patients will be allocated into two groups of equal size.Group A – Arthroscopic assisted C chips graft reconstruction (intervention group), *N* = 44.Group O – Open C graft reconstruction (control group), *N* = 44.

The randomization is done in the outpatient clinic and the patients will be informed about the operative treatment. The randomization is done using an irreversible application in Research Electronic Data Capture (REDCap). Patients will be allocated in a 1:1 ratio by block randomization, stratified for proximal pole fracture (yes /no), dislocation (> / < 2 mm) and smoking (yes/ no). An independent statistician generated the randomization sequence for REDCap, and thus the allocation is concealed to the research staff and physicians.

## Blinding

In this observer-blinded RCT, union is assessed by a blinded musculoskeletal radiologist. QDASH is a patient-reported survey, without the involvement of surgeons or research staff. Other secondary outcomes will be measured by an independent observer. The study will not be blinded to the operating theatre staff, surgeons, physiotherapists or patients.

## Interventions

All patients will be operated on by 4 highly experienced hand surgeons of the same experience level. Two surgeons will perform the open technique and 2 surgeons the arthroscopic technique. The surgeons are using the technique which they are familiar with to avoid a learning curve affecting the outcomes.

## Group A: arthroscopic assisted cancellous chips graft reconstruction

Patients are awake in a supine position with the arm anaesthetized as standard. The arm is attached to a wrist traction tower with vertical traction of 5–8 kg force through plastic finger trap devices. An arm tourniquet is applied. Through 3/4 and 4/5 portals using dry-arthroscopy, the radio-carpal joint is inspected for cartilage damage, synovitis and ligament injuries. Mid-carpal radial (MCR) and mid-carpal ulnar (MCU) portals are applied to examine the non-union site. The non-union site is debrided with a shaver until healthy-looking bone with punctate bleeding. The C chips graft is harvested from the ipsilateral distal radius through a 2 cm incision with a biopsy needle, using multiple biopsy probes. After arthroscopy, the wrist is taken out of traction and the non-union is reduced under the C-arm image intensifier and a 1.2-mm K-wire is inserted percutaneously, either in a retrograde or anterograde manner. The scaphoid is prepared with a drill, the length is measured and the graft is inserted with a trochar through the MCR portal. An Acutrak mini compression screw (Acumed^tm^, Hillsboro, USA) is inserted. The final position is confirmed under fluoroscopy. The non-union site is inspected, and spilled bone graft material is impacted in the gap. Finally, the skin is sutured, and a bandage is applied.

## Group O: open corticocancellous graft reconstruction

Patients are under general anaesthesia with the arm anaesthetized with a regional block anaesthesia. A longitudinal volar incision, lateral to the flexor carpi radialis (FCR) curved distal over the scaphoid tuberosity is made. The FCR is retracted to the ulnar side and the volar capsule and ligaments are incised longitudinally to expose the scaphoid. The non-union is debrided to a healthy-appearing bone. A C graft is harvested from the ipsilateral iliac crest through a 4-cm incision. The cancellous graft is prepared and placed in the cavity. Under fluoroscopy, a 1.2-mm K-wire is inserted in a retrograde or anterograde manner. After drilling, the length is measured and an Acutrak mini compression screw (Acumed^tm^, Hillsboro, USA) is inserted. The final position is confirmed under fluoroscopy. The capsule and ligaments are repaired, the skin is sutured and the immobilizing bandage is applied.

## Physiotherapy and rehabilitation

Rehabilitation will be identical between the groups. Stitches are removed 2 weeks postoperatively. Patients will be provided a thumb/wrist splint for 2 weeks, followed by the application of removable orthosis for another 4 weeks allowing the beginning of light non-weight-bearing exercises. The wrist will be allowed mobilization without restrictions if union is established on a postoperative CT scan and with the absence of scaphoid tenderness on the clinical examination. Return to work will be accepted when the union is established.

### Outcome measures

#### Primary outcome

Time to union will be assessed with repeated CT scans in 2 weeks intervals from 6 to 16 weeks postoperative. If union is not achieved within 16 weeks, a CT scan will be made 24 weeks postoperatively. If union is not achieved at that point, the patient will be presented for another treatment modality. Union will be proclaimed and recorded when > 50% bone bridging occurs on CT scan [26, 27]. The Minimal clinically important differences (MCID) have not been defined. We use an arbitrary value of 3 weeks difference.

#### Secondary outcomes

For *radiographic outcomes*, the union rate will be evaluated with CT scans undertaken every second week. DCA and HLR will be measured preoperative and at follow-up on CT scans to evaluate the correction of deformity [11, 31].

*Pain* at rest and activity is recorded on a visual analogue scale (VAS), ranging from 0 to 10, with 10 reflecting the worst and 0 representing no pain in the wrist.

*Donor site morbidity* located to the iliac crest (Group O) and distal radius (Group A) are evaluated with VAS ranging from 0 to 10, with 10 reflecting the worst and 0 representing no pain in the wrist.

*Range of motion* (ROM) is measured in degrees with a goniometer and recorded in arcs for flexion/extension, supination/pronation and radial/ulnar deviation, compared to the unaffected wrist.

*Grip strength* is measured in kilograms with a Jamar dynamometer with the elbow will be in 90° flexion and attached to the chest compared to the unaffected [32].

*Key pinch* is measured in kilograms using a pinch gauge with the elbow in 90° flexion and attached to the chest, compared to the unaffected wrist [33].

*Patient satisfaction* is evaluated with the following question: What is the function of your hand today, compared to before surgery? With the following answer options: (1) disaster, (2) much worse, (3) slightly worse, (4) unchanged, (5) slightly better, (6) much better, (7) recovered. Second, for future research perspective, patients are asked: when you consider the following parameters: the activities you can carry out in daily life, your pain, your function of the hand, do you think your current situation is satisfactory? (yes/no) [34].

*EQ5D-5L* will be used to estimate the threshold for acceptable cost-utility ratio — the threshold for how much healthcare providers will pay for an extra quality-adjusted life year (QALY). The cost-utility of the arthroscopic and open techniques will be compared. Baseline and 2-year follow-up scores will be compared. A cost model will be defined from patient data, clinical records, and unit costs from the Danish healthcare system. Length of hospital stay, discharge, pain medication usage and readmission will be recorded.

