**Methods:**

Single site, prospective, observer-blinded randomized controlled trial. Eighty-eight patients aged 18–68 years with scaphoid delayed/non-union will be randomized, 1:1, to either open iliac crest C graft reconstruction or arthroscopic assisted distal radius C chips graft reconstruction. Patients are stratified for smoking habits, proximal pole involvement and displacement of > / < 2 mm. The primary outcome is time to union, measured with repeated CT scans at 2-week intervals from 6 to 16 weeks postoperatively. Secondary outcomes are Quick Disabilities of the Arm, Shoulder and Hand (Q-DASH), visual analogue scale (VAS), donor site morbidity, union rate, restoration of scaphoid deformity, range of motion, key-pinch, grip strength, EQ5D-5L, patient satisfaction, complications and revision surgery.

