## Discussion

Today, operative treatment for scaphoid delayed union or non-union is performed with the conventional open technique or the arthroscopic technique based on the preference of the surgeon. Based on non-randomized studies both techniques appear safe and with no major differences in functional outcome or adverse events [16, 35]. There is, however, disagreement regarding the treatment of patients with a large deformity. Hegazy et al. [36] and Sayegh and Strauch [13] found superior correction and superior ROM, Q-DASH and Mayo wrist scores in patients treated with a structural graft compared with patients treated with a non-structural graft. Other studies found no difference in deformity correction [15, 37, 38].

The arthroscopic technique is potentially less invasive with minimal donor site morbidity and potentially faster time to union [15] because of minimal trauma to the ligament structures, joint capsule and the tenuous blood supply [19]. It may also have advantageous osteogenic properties compared to a structural graft [39]. Differences in time to union between the open technique and the arthroscopic technique have, to our knowledge, never been investigated.

X-ray is commonly applied to monitor union after operative treatment for scaphoid delayed/non-union. Consolidation on at least three out of four views is a sign of union [40]. X-ray is not reliable to determine fracture displacement and deformity [41], and the wrong position of the hand and “overlining” in the fracture line can complicate the evaluation of union. CT scans are reportedly more accurate and reliable in the assessment of union [26, 42–44]. We aim to provide a more accurate measurement of time to union with repeated CT scans.

The study differentiates from standard treatment with up to 7 scheduled CT scans in patients with prolonged union time, compared to 1–3 CT scans and 1–3 X-rays as a standard follow-up. The background radiation in Denmark is 3 mSv each year. Each CT scan is performed with the involved wrist above the head with a mean radiation dose of 0.03 mSv. The wrist contains minimal radiation-sensitive red bone marrow and the cumulative radiation dose is maximal 0.21 mSv, (category IIA, international commission on radiation Protection), corresponding to 21 days of background radiation [45]. The radiation dose of each scaphoid X-ray is 0.0002 mSv.

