We aim to decrease observer and selection bias through blinding and randomization, stratified for tobacco-smoking habits, fracture displacement (> / < 2 mm) and proximal pole fractures. By adding 20% to the sample size, we compensate for dropouts and attempt to avoid Type-II errors. Potential dropouts will be minimized with permission to contact patients by mail or phone if they do not show up for follow up-visit or if data is missing.

The patients will not be blinded to their treatment allocation. Sham surgery can be used to blind patients regarding skin incisions and subsequently the surgical technique. However, all patients treated with open bone grafting using a cancellous graft taken from the iliac crest will be operated on in general anaesthesia, while arthroscopically treated patients undergoing the treatment in regional block anaesthesia. Furthermore, the use of graft from the iliac crest in one group and not the other makes it difficult to blind patients as donor-side pain is expected. Finally, we do not expect patients to have an expectation of open- or arthroscopic-assisted graft reconstruction to be superior to the other.

Observer bias is minimized with a blinded musculoskeletal radiologist for the primary outcome, to prevent observer bias from favouring one of the interventions.

The secondary outcome (Q-DASH) is reported by the patient independently, thus with no implication to the assessor. Other secondary outcomes are evaluated by an independent, non-blinded observer.

The current standard treatment at our department includes follow-up until the union is established. In this study, we will have additional follow-up examinations at 6 months and at 1 and 2 years. It has the risk of keeping the patients in the role of being ill. However, the patients can have a feeling of extra good care with the possibility to address uncertainty or problems more easily.

Patients are at risk of being treated inferior with an intervention which is deemed inferior with the study analysis, but nothing a priori suggests which intervention is the better one.

The trial will provide high-quality evidence regarding time to union and short- and long-term functional outcomes of open and arthroscopic assisted graft reconstruction for scaphoid delayed/non-union.

The results from the study can contribute to establish a treatment algorithm for scaphoid delayed/non-union together with results from other studies.

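### The zero point of the donor-site pain scale refers to the wrist, which contradicts the donor sites named in the same sentence and repeats the wrist-pain scale

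*Protocol article*

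**What the plan says.** The abstract of the protocol article names pain and donor-site morbidity as two distinct secondary outcomes: "visual analogue scale (VAS), donor site morbidity, union rate". Under Secondary outcomes, general pain at rest and in activity is scored on a VAS "ranging from 0 to 10, with 10 reflecting the worst and 0 representing no pain in the wrist". The next item is donor site morbidity, "located to the iliac crest (Group O) and distal radius (Group A"), and these sites "are evaluated with VAS ranging from 0 to 10, with 10 reflecting the worst and 0 representing no pain in the wrist".

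The descriptions of the interventions confirm where the grafts come from. For Group O, "A C graft is harvested from the ipsilateral iliac crest through a 4-cm incision". For Group A, "The C chips graft is harvested from the ipsilateral distal radius through a 2 cm incision".

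The Discussion treats donor-site morbidity as a point of contrast between the arms: "The arthroscopic technique is potentially less invasive with minimal donor site morbidity". It also gives anticipated pain at the iliac crest donor site as a reason why patients cannot be blinded.

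**The concern.** The item is meant to measure pain where the graft was taken, but the only body part named on its scale is the wrist. For Group O the sentence contradicts itself, because the iliac crest is not in the wrist. For both groups the scale has the same range and the same anchors as the wrist-pain VAS just before it, so nothing in the scale separates the two items.

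At stake is one secondary comparison, but one that belongs to the trial's rationale. The Background cites greater donor-site morbidity with iliac crest grafts, and the Discussion offers less of it as an advantage of arthroscopy. This VAS is the only donor-site-specific measure that the article describes. The list under Complications and secondary surgery does not name donor-site pain, and EQ5D-5L and use of pain medication are not specific to a site. If the form carries the printed anchor, no other measure described in the article recovers the comparison.

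**Working it through.** The plan gives no figure to reproduce for this point, and no sample-size or power input bears on it. The check is a comparison of texts, followed by a short argument about direction.

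**Step 1: the two items side by side (Secondary outcomes).**

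| | Wrist-pain VAS | Donor-site VAS |
|---|---|---|
| Intended site | wrist | iliac crest (O), distal radius (A) |
| Range | 0 to 10 | 0 to 10 |
| Meaning of 10 | worst | worst (no site named) |
| Meaning of 0 | no wrist pain | no wrist pain |

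Only the intended site differs. The anchors are the same, word for word.

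**Step 2: does another section correct the anchor?** Donor sites or donor-site morbidity also appear in the abstract, the Background, both intervention descriptions and the Discussion. These confirm the sites and the importance of the outcome. None restates or changes the scale.

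**Step 3: what the anchor does if patients follow it literally.**
- Group O, crest pain but no wrist pain: the score is 0 although there is donor-site pain.
- Group O, wrist pain but no crest pain: the score is above 0 although there is no donor-site pain.
- Group A: the harvest incision is at the distal radius, next to the operated wrist, so a wrist anchor cannot separate harvest pain from the pain that the other VAS already records.

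**Step 4: direction of the bias.** Let W_O and W_A be mean wrist pain in the two arms, C_O mean iliac crest pain in Group O, and R_A mean harvest-site pain in Group A.
- Intended contrast (O minus A): C_O − R_A.
- Contrast recorded under the literal reading: W_O − W_A.
- Bias = (W_O − W_A) − (C_O − R_A).

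The bias is negative, and understates the excess donor-site pain in Group O, when C_O − R_A exceeds W_O − W_A. It is positive when the reverse holds. Both arms have an operated wrist, and in Group O the volar capsule and ligaments are opened, so W_O cannot be taken as zero. The article gives none of the four means. Neither sign nor size follows from it.

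**The case against.** The strongest reply is that the intention is clear. The sentence begins by naming the construct and the site for each arm, the abstract keeps pain and donor-site morbidity apart, and the Discussion expects pain from the iliac crest graft. The closing phrase was most likely carried over from the item before it. The article condenses a fuller protocol, the questionnaire is not shown, and the form in use may name the right site.

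Most of this stands, and it rules out three stronger conclusions that a reader might draw:

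- *That the trial does not measure donor-site pain comparably.* The article shows a contradiction in wording. Whether measurement suffers depends on a form that cannot be seen.
- *That the comparison is biased against the arthroscopic arm.* This holds for a Group O patient with crest pain and no wrist pain. It does not hold in general, because wrist pain would be scored in both arms.
- *That the wording accounts for all the overlap in Group A.* Part of it is anatomical. Distal radius donor pain and operative wrist pain lie close together, and some overlap will remain under any anchor.

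The reply does not remove the contradiction itself. The anchor was not left to a fuller document. It is stated, and it does not fit one of the two sites that it is meant to cover.

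**Conclusion.** The point holds as a contradiction within one outcome definition: the zero of the donor-site VAS refers to the wrist, while the same sentence places the outcome at the iliac crest in Group O and the distal radius in Group A. If the questionnaire follows the text, the item misses iliac crest pain in Group O, cannot be told apart from the wrist-pain VAS, and does not support a valid donor-site comparison. The bias would be of unknown direction and size. If the questionnaire already names the donor site, the error is only in the text.

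The consequence is minor: one secondary outcome among many, with no effect on time to union, the sample size or the primary analysis. The conclusion on harm rests on one assumption that the article cannot settle, namely that the form carries the printed anchor.

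**What to change.** 1. Check the questionnaire in use.
2. Define the scale as 0 = no pain at the graft donor site and 10 = worst pain at the graft donor site. Name the site on the form (iliac crest in Group O, the distal radius harvest incision in Group A), and keep the item separate from the wrist-pain VAS.
3. If the form already names the site, correct only the protocol text.
4. If the form used the wrist anchor, correct it, record the date of change, and report the scores collected before it separately with that limitation. Relabelling cannot recover them.

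The change is one line in the protocol and, if needed, one on the form. It is not entirely free. Trial status gives February 15, 2023 as the start of inclusion, so a change of form during the trial would leave scores before and after it that are not comparable. The downside is small, and an early check limits it, since Follow-up has patient-reported outcomes running to 24 months and online questionnaires at 5 and 10 years. In reporting Group A, state that some overlap between harvest-site pain and operative wrist pain remains even with the corrected anchor.

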## Complications and secondary surgery

We will record all complications related to the operative treatment (tendon, ligament, nerve or arterial injury, infection, complex regional pain syndrome, haematoma or hardware failure). Reoperations, defined as revision surgery and secondary surgery due to no union will be noted.

## Follow-up

All patients will be followed for 10 years. Union will be measured in 2 weeks intervals 6–16 weeks after operative treatment. Clinical outcomes and patient-reported outcomes will be measured after 1.5, 3, 6, 12 and 24 months. Online questionnaires will be sent after 5 and 10 years (Fig. 2).

## Protocol violations and patient drop-out

The patients evaluated for inclusion will be reported in a consort diagram (Fig. 3). The statistical analysis will be conducted on an intention-to-treat basis. Outcome scores will be analysed according to the initial study group assignment regardless of possible cross-over. If crossover does occur, a secondary per-protocol analysis will be conducted.

**Fig. 3 Fig3:**
[figure not shown]
Consort flow diagram. Flow of patient through the study

Patients drop-out/loss to follow-up will be recorded and the reason will be noted. The patient is included in the analysis with their latest follow-up if at least a 6-week evaluation is available. Patients who undergo revision/secondary surgery will remain in the study and will be followed according to the index procedure. Their results before and after the revision procedure are included in the analysis. If challenges in the trial conduct occur, they will be presented by the primary investigator every second week to the research group. Any protocol modifications will be communicated to all investigators, observers and trial registries immediately. No regular audit is planned, apart from possible independent inspection visits by the Data Protection Agency and the National Committee on Health Research Ethics.

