#### Data analysis

Interim data analysis will not be carried out. Continuous data will be presented as means with SD or as median with interquartile range (IQR) depending on the nature of data. Categorical data will be presented as counts with percentages. Differences in demographic data and outcome measures between groups will be compared using chi-square for categorical data and Student’s *t*-test (parametric data) or Wilcoxon signed rank test (non-parametric data) for continuous data.

An intention-to-treat analysis will be conducted for the primary outcome. A per-protocol analysis will be conducted to test the non-adherence to the protocol, and patients who do not comply with the protocol will be excluded. Primary outcome will be analysed with a mixed effect model adjusted for fracture location, smoking habits and dislocation (the strata in the block randomization) to account for imbalance in baseline covariates and to improve the power of the treatment effect.

Subgroup analyses for the duration of non-union (< 6 months vs. > 6 months), patients with/without deformity based on the preoperative measurements of HLR and DCA will be performed. It will be clarified if post hoc analyses are carried out. For missing data in an outcome measure, multiple imputation analysis with the covariates: age, smoking, fracture location, dislocation > / < mm and duration of non-union will be conducted to minimize bias of nonresponse. Applied level of significance for all statistical analyses is *P* < 0.05. The statistical analyses will be performed using computerized statistical software.

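### Drop-outs fall under two unreconciled rules, and a 6-week entry condition narrows the promised intention-to-treat analysis

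*Protocol article*

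**What the plan says.** Three statements in the protocol article bear on patients with incomplete follow-up.

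- **Protocol violations and patient drop-out**, opening paragraph: "The statistical analysis will be conducted on an intention-to-treat basis". It goes on: "Outcome scores will be analysed according to the initial study group assignment regardless of possible cross-over". The promise is repeated under Data analysis: "An intention-to-treat analysis will be conducted for the primary outcome". Neither place makes it conditional on a post-operative evaluation.
- **The same section, after the flow diagram**, directly following the sentence on recording drop-outs and their reasons: "The patient is included in the analysis with their latest follow-up if at least a 6-week evaluation is available".
- **Data analysis**: "For missing data in an outcome measure, multiple imputation analysis with the covariates: age, smoking, fracture location, dislocation" and duration of non-union "will be conducted to minimize bias of nonresponse".

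The article does not assign either missing-data rule to particular outcomes, and does not name one as the main analysis and the other as a sensitivity analysis.

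**The concern.** The sentence on drop-outs does two things: it sets a condition for entering the analysis, and it says what the patient enters with. The condition conflicts with intention-to-treat. What the patient enters with conflicts with multiple imputation, or at least is not reconciled with it.

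The week chosen makes this matter. Week 6 is the first CT (Primary outcome), the first clinical and patient-reported visit at 1.5 months (Follow-up), and the end of two weeks of splint plus four of orthosis (Physiotherapy and rehabilitation). Day 42 also precedes the planned mean time to union in both arms, 56 and 77 days (Sample size calculation). A patient whose only evaluation is at week 6 therefore tells us little about final union or function.

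Three things are at stake: who is in the primary analysis set, which value a drop-out contributes, and whether the choice between the rules could be made after results are seen.

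**Working it through.** **1. The rules side by side**

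| Patient | Drop-out rule | Intention-to-treat and imputation rules |
|---|---|---|
| Lost before week 6 | Not analysed | Kept in the randomised arm, outcome imputed |
| Lost after the week-8 CT, not united | Analysed with the latest follow-up | Union time missing, imputed |
| Lost after the 3-month visit, 24-month Q-DASH missing | Analysed with the latest follow-up | 24-month score imputed |

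The first row is a direct conflict. In the other two rows the rules differ if the latest follow-up supplies the patient's result. They agree only if the drop-out sentence is taken to mean that visits up to drop-out are used and the rest imputed, which it does not say.

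**2. Patients removed by the 6-week condition**

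The article does not say when its 20% drop-out would occur. With 44 per arm, 0.20 × 44 = 8.8, so the condition could remove between 0 and about 9 patients per arm, depending on how much of that drop-out falls before week 6.

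**3. Effect on time to union if the last CT date is used as the result**

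*Inputs from the article:* Group A mean 56 days, SD 30. The other group (labelled B in the sample size text, taken here as Group O) mean 77, SD 40. CT at weeks 6, 8, 10, 12, 14 and 16, then week 24 if not united. Planned difference: 77 − 56 = 21 days.

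*Assumptions not in the article:* lognormal healing times; the last CT of a drop-out equally likely at each scan from week 6 to 16; no drop-out before week 6; patients not united by week 24 set to 168 days.

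*Formulas:* σ² = ln(1 + (SD/mean)²) and μ = ln(mean) − σ²/2.

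- Group A: σ² = ln(1 + (30/56)²) = 0.252, μ = 3.899
- Group O: σ² = ln(1 + (40/77)²) = 0.239, μ = 4.224

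Each time is moved to the first scan at or after it. A drop-out not united at the last scan is given that scan's date.

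| Drop-out A / O | Mean difference (days) |
|---|---|
| none | about 20.5 |
| 5% / 5% | about 20 |
| 10% / 10% | about 19.2 |
| 20% / 20% | about 18 |
| 10% / 30% | about 15 |
| 30% / 10% | about 21 |

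At 20% in both arms, about 5% of Group A and 9% of Group O receive a last-CT date in place of a healing time. The shrinkage is (20.5 − 18)/20.5 = 12%.

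**4. Sensitivity of the illustration**

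Gamma times on the same scan grid give about 21 falling to about 18 days at 20% / 20%. Gamma times without the grid, with every drop-out last seen on one fixed day between 42 and 70, start from 21 days and give 17.5 to 18.5 (20% / 20%), 11.8 to 16.0 (10% / 30%) and 21.2 to 23.1 (30% / 10%). Under this reading each affected patient's time is understated, but the difference between arms can move either way.

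**The case against.** The strongest reply is that carry-forward is inferred. The sentence never says that an early value replaces a later one. It can be read as defining who enters and up to which visit their data count, with imputation supplying the rest. Two features favour this: the primary analysis is called a mixed effect model, and the next lines of the section keep results from both before and after revision surgery. Likewise, union is recorded only once bridging exceeds 50% on CT, so a drop-out without union has no recorded union time and would be a candidate for imputation. This stands. A reader might infer that the article plans to carry the last observation forward and to enter last-CT dates as healing times; the text permits that but does not state it.

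A second reply is that the section explains intention-to-treat only through group assignment under cross-over, so the 6-week condition merely yields a modified intention-to-treat set. But the article does not call it modified, and the promise for the primary outcome carries no such limit.

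A third reply concerns size. The 12% shrinkage puts the whole 20% allowance inside the CT window and splits it equally, whereas follow-up runs to 24 months and beyond, and a patient lost after union does not affect the primary outcome. This also stands. A reader might infer that the rule always dilutes the treatment difference; the unequal cases show that it need not.

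Finally, an analysis plan that is not shown may settle the details. That would answer silence. Here the article states both rules, so a plan would have to override or reinterpret one of them.

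**Conclusion.** The concern holds in this form: the 6-week condition removes randomised patients despite the intention-to-treat promise, and the latest-follow-up rule stands beside multiple imputation with no statement of which governs. Confidence in that conflict is high. It does not depend on the simulation, and the milder reading does not remove the 6-week exclusion.

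The consequences for the estimates are conditional, with medium confidence. They require that the last visit serve as the patient's result. For time to union the loss then ranges from about half a day (5% in each arm) to about 2.5 days (20% in each arm) out of about 20.5. With unequal drop-out the difference lies between about 15 and 21 days, or about 12 to 23 if drop-outs all leave early. Unequal drop-out is possible because patients are not blinded, but nothing in the article predicts it. The effect of the 6-week exclusion itself cannot be estimated from the article. For functional outcomes, a score from the end of the orthosis period could stand for any later visit up to 24 months; the article gives no figures from which to size that.

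**What to change.** - Delete the latest-follow-up rule and its 6-week condition.
- State that all randomised patients stay in the intention-to-treat analysis, in their assigned arm.
- For time to union, treat a patient without union at the last CT as censored at that scan, not as united on that date. The primary model must then accept censored times; if union times are imputed instead, the imputed value must lie after the last scan without union.
- For Q-DASH, pain, motion and strength, use all observed visits and handle missing values by one rule: the multiple imputation already described, or a likelihood-based mixed model.
- If a last-visit analysis or a set restricted to patients with a 6-week evaluation is still wanted, label it as a sensitivity analysis.

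The cost is a text change in the protocol and in any analysis plan, made before outcome data are analysed by arm. Visits, scans and data collection do not change.
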